**Methods/design:**

This field trial is located at primary care centers. The participants are adults aged 29 to 66 years, with a Body mass Index (BMI) between 29 and 40.99 kg/m^2^ and without diabetes. To date, 245 participants have been assigned randomly to the low-fructose diet intervention group (LFDI) at health centers in the western health service zone of Tenerife island, and 245 to the standard-diet control group (SDC) at health centers in the eastern health service zone. Recruitment is opportunistic and is carried out by physicians and nurses at participating health centers. Initially (baseline), and after 24 weeks of intervention, dietary records, physical activity, waist circumference, BMI, blood pressure, fasting blood glucose and insulin concentrations (HOMA2-IR) and lipid profile are recorded; blood glucose and insulin and lipid profile are also recorded 2 h after a 75-g glucose overload. After 48 weeks (24 weeks after the intervention), fasting blood samples are again obtained and a physical examination is performed. All tests and measures are repeated and recorded except dietary records, physical activity and oral glucose overload. Low-fructose diets are designed by calculating free and total (free + fructose associated with sucrose) fructose contents in standard diets, and removing foods with a fructose content in the highest quartile for the amounts in the standard diet.

Participants in both groups are prescribed a diet that contains 30 to 40% less than the participant’s energy requirements. The primary endpoint is change in HOMA2-IR between baseline and week 24, and other outcomes are change in HDL-cholesterol, LDL-cholesterol, triglycerides , waist circumference to height ratio and BMI. The secondary endpoint is change in HOMA2-IR between week 24 and week 48 together with the outcomes noted above. Comparisons between groups for variables used to indicate IR levels are done with a Student’s *t* test for unpaired variables or the Mann-Whitney *U* test if the distribution is not normal. Multivariate regression models will be used to control for confounding factors not accounted for in the study design, and for independent prognostic factors.

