### Design

A single-blind, multicenter, randomized controlled **f**ield trial with two groups of participants (low fructose/sucrose diet versus standard diet) recruited at primary care health centers in Tenerife island (Canary Islands, Spain). Sample size: because of the lack of consensus in the academic literature regarding the cutoff value of HOMA2-IR that defines the presence of IR, we opted to use body weight change. We estimated a mean weight loss of 4 kg (1.43 kg/m^2^ BMI assuming a mean height of 1.67 m for the Canary Islands’ population [16]), a significance level of *p* ≤ 0.05, 80% power and a 20% dropout/loss to follow-up rate. A weight loss of 4 kg was estimated based on maximum weight loss in the only interventional trial reported to date of the effect of lower fructose consumption on body weight and IR [15]. Dietary intervention trials aimed at studying weight loss have reported similar amounts of weight loss after 6 months [17]. In the trial reported here, in which both groups consume an isocaloric diet, we do not anticipate differences between the groups in the amount of weight lost. Based on these calculations our estimated sample size for each of the two groups is 245 participants.

The primary outcome measure is insulin resistance (IR) which is estimated from fasting serum glucose and insulin concentrations with the computer-based Homeostasis Model Assessment system (HOMA2-IR) at baseline, 24 and 48 weeks. The secondary outcomes are BMI, waist circumference (waist to height ratio) and blood pressure which are measured at baseline, 4, 8, 12, 16, 20, 24 and 48 weeks, and total cholesterol, HDL-cholesterol, LDL-cholesterol and triglycerides which are measured at baseline, 24 and 48 weeks.

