## Discussion

The aim of this study is to evaluate the effectiveness of a low-fructose/sucrose diet compared to a standard diet in lowering IR in obese patients without DM after an intervention period of 24 weeks. Overall reductions in fructose/sucrose consumption are evaluated with no distinction between added sweeteners and sugar naturally present in foods. A diet low in foods with natural fructose content is prescribed for the intervention group, but participants in both groups are instructed to refrain from consuming foods with added sugar. This approach is used because it reflects the usual care offered at participating health centers, and in an effort to ensure comparable food intakes in kcal/day in both groups. To evaluate the difference in fructose intake our reference is the mean value from four daily food diary records from the end of the intervention period (week 24) compared to four daily food diary records at week 0. Although the evidence at present is insufficient to claim that four food diaries are sufficient to provide a reliable analysis of fructose or sucrose intakes, most studies that have estimated these intakes to date have used 24-h recall or (usually four) food diaries [27].

At present, the amount of fructose intake that could be harmful to health is unknown. A trial such as this one, carried out in the primary care setting, should provide valuable information for future efforts to control IR. Because the restricted calorie diet prescribed for our participants is similar in both groups, we expect to see similar weight reductions in both. Our hypothesis is that under our trial conditions, the reduction in IR will be greater in the group with the low-fructose diet than in the SDC. Accordingly, if the dietary intervention being tested, i.e., a diet low in fructose/sucrose, is able to reduce IR, the results – if translated into regular clinical practice – could provide a hitherto unavailable tool to prevent type-2 DM.

A potential limitation of this type of study is the likelihood that many participants will under-report some of their food intakes, as has been shown for persons with obesity. We will analyze the energy intake:basal metabolic rate ratio with a cutoff value of 1.16 for women and 1.19 for men to determine whether participants are under-reporting any food intakes [28].

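### The 245 per group and 80% power are derived from a 4 kg weight loss on which the arms are expected not to differ, so the stated power is unsupported for the HOMA2-IR primary comparison

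*Protocol article*

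**What the plan says.** The abstract (Methods/design) defines the endpoint: "The primary endpoint is change in HOMA2-IR between baseline and week 24". The Design section also names HOMA2-IR as the primary outcome measure. The Statistical analysis section compares IR variables between groups with an independent-samples t test, or a Mann-Whitney U test if the distribution is not normal, two-sided at 5%.

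The sample size paragraph in Design uses another variable. Citing a lack of consensus "regarding the cutoff value of HOMA2-IR that defines the presence of IR, we opted to use body weight change", it continues: "We estimated a mean weight loss of 4 kg". It equates this with 1.43 kg/m² at a mean height of 1.67 m and adds "a significance level of *p* ≤ 0.05", 80% power and 20% loss, arriving at 245 per group. The source of the effect is given as follows: "A weight loss of 4 kg was estimated based on maximum weight loss in the only interventional trial reported to date".

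Just before the result, the paragraph states that "we do not anticipate differences between the groups in the amount of weight lost". The Discussion repeats the expectation ("we expect to see similar weight reductions in both") and places the hypothesised effect elsewhere: "the reduction in IR will be greater in the group with the low-fructose diet than in the SDC". The article gives no HOMA2-IR difference or SD, no SD for weight, and no link from 4 kg to a difference in HOMA2-IR.

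**The concern.** The reason given for leaving HOMA2-IR does not apply to this endpoint. A cutoff is needed to size a comparison of proportions above or below it. A continuous change needs a mean difference and an SD.

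The substitute cannot stand in for the primary contrast either. The primary objective is an IR effect independent of a reduction in calorie intake, and the hypothesis is a greater fall in IR with similar weight loss in both arms. Weight is therefore the variable on which the arms are meant not to differ.

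What is at stake is how the result is read. If the HOMA2-IR comparison is null, readers will weigh it against the published 80% power as evidence that no worthwhile effect was missed. The plan does not show that the design has that property for HOMA2-IR.

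**Working it through.** **Inputs from the article.** 4 kg; height 1.67 m; α = 0.05 (two-sided, from Statistical analysis); power 80%; loss 20%; 245 per group; 16 centers, with one zone per arm (Randomization). No SD is given.

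**1. The plan's own figures.** 4 / 1.67² = 1.434 kg/m², which agrees with the stated 1.43. The 245 cannot be reproduced because the SD is missing, so I solved for the SD it implies. Completers per arm are 245 × 0.8 = 196. In the two-sample formula n = 2(1.96 + 0.842)² (SD/δ)², with δ = 4 kg and n = 196:

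SD = (4 / 2.802) × √(196/2) ≈ 14.1 kg (5.05 kg/m² on the BMI scale).

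Other conventions imply other values: 14.4 kg if 20% was added rather than divided out, 15.8 kg with no dropout allowance, 15.9 kg for a one-sided test, and 20.0 kg for a paired or one-sample test. The article does not say which was used.

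**2. The two readings of the 4 kg.**
- *Between-arm difference.* The formula then powers a 4 kg contrast in weight. The plan expects that contrast to be about 0 kg. At a true difference of zero the rejection rate is α = 5% whatever the sample size, and no finite number gives 80% power.
- *Within-arm change.* The formula then sizes a before-after test in one arm and says nothing about a comparison between arms.

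Neither reading involves HOMA2-IR.

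**3. What the sample can detect on HOMA2-IR.** In SD units of HOMA2-IR change, with independent participants, the detectable difference is d = 2.802 × √(2/n).
- n = 196: d = 0.283 (0.284 by noncentral t).
- n = 245: d = 0.253 (0.254 by noncentral t).

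Power at 196 per arm over an assumed range of true differences:

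| True difference (SD) | 0.10 | 0.15 | 0.20 | 0.25 | 0.30 | 0.40 |
|---|---|---|---|---|---|---|
| Power | 17% | 32% | 51% | 70% | 84% | 98% |

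**4. Sensitivity to clustering (illustration only).** Assume 8 equal centers per arm, so 196/8 = 24.5 completers per center, a design effect of 1 + 23.5 × ICC, and 16 − 2 = 14 df. Then d = (2.145 + 0.868) × √(2 × design effect / 196).

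| Assumed ICC | Design effect | Detectable difference |
|---|---|---|
| 0.01 | 1.235 | 0.34 SD |
| 0.02 | 1.47 | 0.37 SD |
| 0.05 | 2.175 | 0.45 SD |

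The article gives neither the split of the 16 centers between arms nor their sizes.

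**The case against.** The strongest reply is that the article is open about sizing on weight and never writes 80% power for HOMA2-IR in so many words. No arithmetic is wrong: the BMI conversion is right, and 245 cannot be faulted because its SD is not shown, which a condensed article may leave to the full protocol. Enrolment, the estimate, the test and the type I error are all unaffected.

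Much of this stands. This is a fault of justification, not of arithmetic, and the missing SD is not held against the plan. But condensation does not explain the contradiction. The article itself states the basis of the sample size and the expectation that defeats it, and it offers no other power for the primary endpoint.

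Some stronger statements are tempting and are not supported:
- *The 4 kg is a within-arm loss in the cited trial.* The article says only that it was the maximum weight loss there, and that source is not at hand. The point holds under either reading.
- *The implied 14.1 kg is an SD of body weight wrongly used for weight change.* That is a guess. The implied value ranges from 14.1 to 20.0 kg with the convention used.
- *The trial's real detectable difference is 0.34–0.45 SD.* Those figures need independently allocated, equal centers and a 14-df analysis. The article allocates one zone to each arm and plans individual-level tests.

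The 196 is also a completer count. The intention-to-treat analysis carries forward the last available measurements, so up to 245 per arm may be analysed. Carried-forward values may dilute an effect, so the larger count is not necessarily an advantage.

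**Conclusion.** The point holds as a failure of justification: no reading of the sample size paragraph makes 80% the power of the primary comparison. A reader might infer that the trial is too small. The documents do not show that, because they give no HOMA2-IR difference or SD to judge it by. If the true difference is about 0.28 SD or more and participants are independent, 196 completers per arm do give 80% power. At 0.20 SD they give about half.

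The range of 0.25–0.28 SD (245 or 196 per arm) rests on independence and is a best case. Any positive correlation within centers enlarges the detectable difference. Because arm coincides with zone, no center-level ICC accounts for a difference between the zones themselves. The true differences and ICCs in the working are assumptions shown as ranges.

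**What to change.** Rewrite the sample size paragraph in Design.

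1. Keep the 4 kg text only as the history of how the number was chosen, and state that it does not size the HOMA2-IR comparison. The abstract reports 245 already assigned to each group, so the record of the original basis should not be erased.
2. Replace the 80% claim with wording such as: *With 196 completers per arm (245 less 20%) and a two-sided 5% test, the trial has 80% power for a between-arm difference in HOMA2-IR change of about 0.28 SD (0.25 SD if all 245 per arm are analysed), assuming independent participants.*
3. Convert this to HOMA2-IR units with the pooled, arm-blind SD of the change when it is available. The article does not say how much week-24 data exist.
4. Label the figure a best case. Say that correlation within centers enlarges it, for example to about 0.34–0.45 SD at assumed ICCs of 0.01–0.05 with 8 equal centers per arm, and that even this does not cover a zone effect, since each arm is one zone.

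The cost is one paragraph and a less favourable stated figure. It requires no extra patients and no change to endpoint, test or treatment.

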### Statistical analysis

Before-after changes in IR, laboratory indicators and anthropometric values are determined with Student’s *t* test for paired samples. Comparisons between the intervention and control groups for variables indicative of IR are done with Student’s *t* test for independent samples when the frequency distribution is normal, or with the Mann-Whitney *U* test when the distribution is not normal. For these comparisons multiple linear or regression models are used as appropriate to detect possible confounders or independent prognostic factors for IR that are not controlled for in the trial design. Student’s *t* test for paired samples will be used to analyze changes between week 0 and week 24 in the main outcome variables in each group (HOMA2-IR, fasting blood glucose and insulin, and these same measures after an oral glucose overload) and the secondary outcomes (fasting LDL-cholesterol, HDL-cholesterol and triglycerides, and these same measures after a glucose overload; waist circumference, waist to height ratio, BMI and blood pressure). To verify compliance with the recommended diets the same analysis will be done for total calorie intake and individual nutrient intakes. These analyses will record results for the variables noted above between week 24 and week 48, and between week 0 and week 48. Student’s *t* test for independent samples will be used to analyze the differences between groups observed from week 0 to week 24 for the variables noted above. As potential confounders we will consider calorie intake, variations in nutrient intakes other than fructose, and physical activity. If differences are detected between groups at the start of the study in HOMA2-IR, any nutrient intake or physical activity, appropriate adjustment will be used in the outcomes analysis. An intention-to-treat analysis will be done taking into account losses to follow-up, and using the most recent changes and measurements available for participants who did not complete the study. All hypothesis tests will be two-sided with a significance level of *p* < 0.05, and all statistical analyses will be done with the NT Professional v. 21.0 (IBM) statistical package (SPSS) for PCs in a Windows environment. More specific information about the trial and protocol is summarized in the Standard Protocol Items: Recommendations for Interventional Trials (SPIRIT) Checklist (Additional file 5).

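### For BMI, waist and blood pressure, carrying a dropout's last value forward biases the week-24 comparison, although the interim visits would support a repeated-measures analysis

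*Protocol article*

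**What the plan says.** The Design section of the protocol article lists BMI, waist circumference (as waist to height ratio) and blood pressure as secondary outcomes, "measured at baseline, 4, 8, 12, 16, 20, 24 and 48 weeks". HOMA2-IR and the lipids are taken only at baseline, 24 and 48 weeks. The sample size paragraph allows for "80% power and a 20% dropout/loss to follow-up rate".

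The Statistical analysis section names these analyses:

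- Paired t tests within each arm for week 0 to week 24, then extended: "These analyses will record results for the variables noted above between week 24 and week 48, and between week 0 and week 48".
- An independent-samples t test that "will be used to analyze the differences between groups observed from week 0 to week 24 for the variables noted above".
- Regression, in which "multiple linear or regression models are used as appropriate to detect possible confounders or independent prognostic factors for IR". This concerns insulin resistance. It is not a longitudinal model of BMI, waist or blood pressure.
- An intention-to-treat analysis that allows for losses by "using the most recent changes and measurements available for participants who did not complete the study".

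The natural reading of the last item is that the last observation is carried forward. The values at weeks 4, 8, 12, 16 and 20 therefore enter the named analyses in one way only: as the substituted final value of a participant who leaves.

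**The concern.** Both arms are on an energy-restricted diet, so BMI and waist should still be falling between week 4 and week 24. A participant who leaves at week 8 is analysed as if the week-8 value were the week-24 value. A participant who leaves before week 4 is analysed as if nothing had changed. Both are understatements of the change expected at week 24, and the understatement is larger in the arm that loses more people.

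This matters because the article expects no difference in weight loss between the arms (Design and Discussion) and seeks an effect on insulin resistance independent of calorie reduction (primary objective). The BMI contrast between arms is a natural check on that expectation, and the last-value rule can hide a difference there or create one. Unequal dropout is plausible, since the arms follow different diets at different health centres. The same rule gives anyone lost after week 24 a change of exactly zero from week 24 to week 48.

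**Working it through.** **Inputs from the article.** 245 participants per arm; 20% dropout; visits every 4 weeks from 0 to 24; mean weight loss 4 kg; mean height 1.67 m. The article's BMI equivalent reproduces: 4 / 1.67² = 1.434, stated as 1.43 kg/m².

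**Assumptions, not in the article.** Dropout is spread evenly over the six 4-week intervals to week 24, so the last visit attended is 0, 4, 8, 12, 16 or 20 with equal probability. Change is linear to week 24. Dropout rates by arm and within-person correlations are illustrative.

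**1. Change missed per dropout.** The mean last visit is (0 + 4 + 8 + 12 + 16 + 20) / 6 = 10 weeks. The fraction of the 24-week change that is missed is 1 − 10/24 = 3.5/6 = 0.583.

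**2. Shrinkage of a true difference, equal dropout.** 0.20 × 0.583 = 0.117, or about 12%. A simulation with assumed BMI variances (person SD 2.8, slope SD 1.2, visit SD 0.35) agrees: a true difference of −0.40 kg/m² came back as −0.36 under the last-value rule and −0.40 under a repeated-measures model.

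**3. False difference, unequal dropout and equal true loss.** Bias = (difference in dropout rates) × 0.583 × (mean change).

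- 15% against 25%: 0.10 × 0.583 × 1.43 = 0.08 kg/m². The simulation gave about 0.07, or 0.6 of a standard error; the repeated-measures model gave 0.00.
- 10% against 30%: 0.20 × 0.583 × 4 = 0.47 kg, and 0.47 / 1.67² = 0.17 kg/m².

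**4. Precision of the week-24 contrast.** Generalised least-squares variances were computed for 245 per arm with ignorable dropout. The within-person correlation was compound symmetry (0.7 or 0.9), autoregressive (0.90, 0.95 or 0.98 per 4 weeks) or random slope. The table gives ratios of standard errors; below 1 favours the repeated-measures model.

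| Dropout | Against baseline-adjusted week-24 analysis | Against change-score t test in completers |
|---|---|---|
| 0% | 1.000 throughout | 0.875 to 0.996 |
| 20% | 0.956 to 0.977 | 0.844 to 0.956 |
| 30% | 0.929 to 0.964 | 0.825 to 0.933 |

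The first column isolates what the interim visits add: nothing with complete data, and about 2 to 4% at 20% dropout. The 0% entry in the second column is the effect of baseline adjustment alone. Where the gain over change scores is large, most of it comes from that adjustment. Where within-person correlation is very high, the interim visits supply more of the gain, but the total is then only about 4 to 7% at 20% dropout.

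**The case against.** The strongest reply is that little is lost. Weeks 4 to 20 are counselling visits, so taking these measurements is not itself a fault. A longitudinal model for secondary outcomes is often left to a separate analysis plan. The two-point contrast already tests for a difference at week 24, and pace of weight loss is not a stated objective. The false difference at 15% against 25% dropout is about 0.08 kg/m², roughly 0.2 kg at 1.67 m, and the article gives one overall dropout rate, not rates by arm.

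Most of this stands and limits the importance of the point. It does not remove it, because the article is not silent: it fixes both the tests and the last-value rule.

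Three stronger readings are tempting, and the article supports none of them.

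- *The plan throws away precision.* A reader might infer this from five visits that no test models. The larger apparent gains arise against change scores in completers, whereas the article plans an intention-to-treat analysis with substituted values. The model's standard error would be slightly larger than that of the last-value analysis, which is artificially small. The fault is bias.
- *The interim values are unused.* They enter through the last-value rule.
- *The primary result is affected.* HOMA2-IR is not measured between baseline and week 24, so modelling weeks 4 to 20 of these outcomes leaves its comparison unchanged.

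A further objection is that the figures above treat participants as independent, whereas arms are assigned by health zone across 16 centres. With 490 / 16 ≈ 31 per centre and an assumed intraclass correlation of 0.01 to 0.05, the design effect is 1 + 30 × 0.01 = 1.3 to 1 + 30 × 0.05 = 2.5. Standard errors would then rise by roughly 14 to 57%, far more than the 2 to 4% above. This stands: the model must account for centre, and no model of this kind cures allocation by zone.

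**Conclusion.** The point holds as a minor one about missing data in secondary outcomes. The last-value rule attenuates a true week-24 difference by about 12% at the planned 20% dropout, and it produces a false difference of about 0.08 to 0.17 kg/m² under the two illustrative splits of dropout by arm. These sizes rest on evenly spread dropout, a linear course and assumed rates by arm. Later dropout, or weight loss concentrated in the early weeks, would make them smaller. The direction of the shrinkage under equal dropout does not depend on the exact timing, so long as the difference between arms is still growing when people leave. The precision gained from the interim visits is a small addition and does not carry the argument.

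**What to change.** In the Statistical analysis section, make the main analysis of BMI, waist measures, systolic pressure and diastolic pressure one mixed model for repeated measures per outcome:

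- Responses: all post-baseline visits (weeks 4, 8, 12, 16, 20, 24 and 48).
- Terms: arm, visit, arm by visit and baseline value, with unstructured within-person covariance and health centre accounted for.
- Result reported: the arm contrast at week 24.
- Sensitivity analysis: the t test with last values substituted. Dropout by arm and visit should be shown beside it.

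The cost is a change of wording and a few lines of code; no new data are needed. There are two downsides. The model assumes that dropout depends only on observed values, and its standard error will be slightly larger than the artificially small one from the last-value analysis. The change leaves the HOMA2-IR comparison and the allocation by zone as they are.
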